#### Exploratory aim 3a

Determine trajectories of child depressive symptoms (CDI), anxiety (RCMAS), and parental stress (PCQ) from baseline to 12-month follow-up. Aim 3a will initially be evaluated using random coefficients models using equations such as:$$ CD{I}_{ij k}=\left({\beta}_0+{\beta}_{0i}+{\beta}_{0k}\right)+\left({\beta}_1+{\beta}_{1i}+{\beta}_{1k}\right)\times Tim{e}_{ij}+{\sum}_{\mathrm{j}=1}^{\mathrm{J}}{\beta}_j Co{v}_{ji}+{\epsilon}_i $$where coefficients without subscripts represent fixed effects, coefficients indexed by i represent individual-level random effects, subscripts indexed by j represent time effects, and subscripts indexed by k represent treatment group differences. Evidence in favor of our hypothesis would be indicated by a significant negative coefficient for β_1k_ for CDI, RCMAS, and PCQ.

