**Methods:**

A sample of 172 African American families will be enrolled from two diverse oncology centers (Helen Graham Cancer Center in Newark, DE, and Kimmel Cancer Center in Philadelphia, PA). Eligible families will be randomized either to a 5-session intervention Families Fighting Cancer Together (FFCT) or a 5-session parent-only psycho-educational (PED) program. Assessments will occur at weeks 0 (baseline), 8 (end-of-treatment), 24, and 52.

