### Statistical power

Sample size was determined from pilot study data for the primary outcome (child depressive symptoms on the CDI) and endpoint (post-treatment) using power = 8 and α = .05 [27]. For all other analyses, minimum detectable effects are presented for fixed sample size. Pilot data indicate a greater decrease in depressive symptoms from pre-treatment to post-treatment among children in the FFCT intervention compared with children receiving PED equivalent to an effect size of Cohen’s d = 0.38, and pre-post correlations of 0.68. This suggests that a sample size of 60 families per study arm will yield power ≥ .8 with α = .05. Conservatively assuming retention of 70% (retention in the single site pilot was 85%), this indicates that recruitment of 172 study participants will ensure adequate statistical power for testing the primary study aim.

For tests of differences at post-treatment, a total sample size of 120 is used. Minimum detectable effects (in SD units) vary as a function of the correlation between pre-treatment and post-treatment measures and range between 0.31 for a correlation of 0.8 and 0.51 for a correlation of 0.2. Test of differences at 12-month follow-up assume that 80% of participants at post-treatment are retained to follow-up but benefit statistically from two additional occasions of measurement. Minimum detectable effects (in SD units) vary as a function of the correlation between pre-treatment and follow-up measures and range between 0.28 for a correlation of 0.8 and 0.38 for a correlation of 0.2.

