### Randomization

Randomized permuted blocks will be used to allocate groups of parent-adolescent dyads to each study arm (FFCT or PED). The data manager will prepare complete sets of allocations which will be placed in sequentially numbered sealed opaque envelopes containing treatment assignments for each group of 5 to 8 families. Once 5 families are recruited, group allocation will be made after a week has elapsed without any additional family participants recruited or once 8 families have been recruited, whichever occurs first.

The assessment team will be blind to the allocation condition and know only the serial numbers. At randomization, following baseline assessments, only the program manager opens the envelope for the group’s allocation. This approach provides both dynamic balancing and prospective partial blinding of the project manager to treatment assignment. At the end of the study, unused sealed envelopes will be retained along with the log to assure that randomization has been carried out as assigned.

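### The example Aim 3a trajectory equation lets the arms differ at a baseline measured before randomisation, which costs precision (modestly at the pilot correlation) but does not invalidate the test

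*Protocol article*

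**What the plan says.** The Protocol article, Exploratory aim 3a, sets the task as "Determine trajectories of child depressive symptoms (CDI), anxiety (RCMAS), and parental stress (PCQ) from baseline to 12-month follow-up", so the week 0 score is the first outcome of the trajectory. The printed equation has a fixed, an individual and an arm component in both intercept and slope. Its key reads "and subscripts indexed by k represent treatment group differences". β0k is therefore an arm difference in intercept and β1k an arm difference in slope. The covariates are not named, and no constraint to a common baseline mean appears.

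The decision rule uses the slope alone: "Evidence in favor of our hypothesis would be indicated by a significant negative coefficient for β_1k_ for CDI, RCMAS, and PCQ". The model is offered as a first step and an example: "Aim 3a will initially be evaluated using random coefficients models using equations such as".

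The Randomization section fixes the order of events: "At randomization, following baseline assessments, only the program manager opens the envelope". The abstract gives the visits: "Assessments will occur at weeks 0 (baseline), 8 (end-of-treatment), 24, and 52". Primary aim 1 and Secondary aim 2 both adjust for the baseline score by ANCOVA.

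**The concern.** Because baseline precedes allocation, randomisation makes the expected arm difference at week 0 zero. An equation that estimates this difference anyway spends information on a quantity already known. It also separates the slope contrast from the baseline adjustment used for the same CDI and PCQ scores in Aims 1 and 2.

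Two things follow. The slope contrast has a larger variance than the same data allow. And once a chance baseline gap has occurred, regression to the mean tilts the slope of the arm that started higher downward, in the direction that counts as benefit. β1k is the only stated criterion for three outcomes, and Exploratory aim 3b extends the preceding models to effect modification, so the choice carries forward.

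**Working it through.** **Inputs.** From Statistical power: d = 0.38, r = 0.68, 60 evaluable families per arm, 80% of these retained to 12 months (48 per arm), 70% retention to post-treatment. From the abstract: weeks 0, 8, 24, 52. Assumed here: two-sided α = 0.05, power 0.8, unit SD at each visit, compound symmetry unless stated, and no clustering by treatment group.

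**1. The plan's own figures.**
- ANCOVA sample size: 2 × (1.960 + 0.842)² × (1 − 0.68²) / 0.38² = 58.4, so 59 per arm. Power at 60 is 0.81, and 120/0.7 gives 172. The plan's numbers reproduce. An unadjusted change score would need 2 × (1.960 + 0.842)² × 2(1 − 0.68) / 0.38² = 69.6, so 70 per arm.
- 12-month detectable effects, stated as 0.28 (r = 0.8) to 0.38 (r = 0.2). For the mean of three follow-ups adjusted for baseline, 2.80 × √(2/48) × √((1 + 2r)/3 − r²) gives 0.272 and 0.374, which is close.
- Other analyses do not match as well:

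| Analysis | r = 0.8 | r = 0.2 |
|---|---|---|
| Stated | 0.28 | 0.38 |
| Mean of three follow-ups, baseline-adjusted | 0.272 | 0.374 |
| Mean of three follow-ups, unadjusted change | 0.295 | 0.591 |
| Slope at week 52, arm-specific intercepts | 0.326 | 0.647 |
| Slope at week 52, common baseline mean | 0.317 | 0.523 |

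The two slope rows use 60 per arm falling to 48 at week 52.

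**2. Variance of the slope contrast.** Put x = week/52. Then Σx = 84/52 = 1.6154 and Σx² = 3344/2704 = 1.2367. With n per arm:
- Arm-specific intercepts: variance = (2/n)(1 − r)/A, where A = Σx² − (Σx)²/4 = 0.5843.
- Common baseline mean: variance = (2/n)(1 − r)/B, where B = Σx² − r(Σx)²/(1 + 3r).
- The ratio of common to arm-specific is A/B.

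| r | B | A/B | Variance cut |
|---|---|---|---|
| 0.2 | 0.9105 | 0.642 | 36% |
| 0.68 | 0.6530 | 0.895 | 10.5% |
| 0.8 | 0.6227 | 0.938 | 6% |

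At r = 0.68 with 60 complete per arm, the standard error falls from 0.135 to 0.128. With 48 at week 52 it falls from 0.147 to 0.140, and the detectable effect from 0.412 to 0.391 SD. With assumed random slopes (SD 0.3 or 0.5 per 52 weeks, intercept-slope correlation 0 or −0.4), the arm-specific version has a variance 7% to 26% larger.

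**3. Effect of a chance baseline gap.** Under no treatment effect, a gap c at week 0 implies expected later gaps of rc. The mean of x is 0.4038. The fitted week 52 slope contrast with arm-specific intercepts is −c(1 − r) × 0.4038/0.5843 = −0.691c(1 − r).
- At r = 0.68 this is −0.22 SD per 1 SD gap.
- One standard error of the gap is √(2/60) = 0.183 SD, so the shift is about −0.04 SD, or 0.30 of the slope's standard error (0.040/0.135).
- A gap of two standard errors gives a conditional type I error of about 0.08.
- With a common baseline mean the shift is zero.

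**4. Over all randomisations.** In 200,000 simulated null trials (r = 0.68, 60 complete per arm), the arm-specific version had mean slope difference zero and type I error 0.050.

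**5. If the true effect is not linear.** Take an arm difference of 0, d, d, d at the four visits, with r = 0.68. The arm-specific fit gives slope 0.691d, z = 0.691d/0.1351 = 5.1d. The common-baseline fit gives slope 1.6154d/(3.04 × 0.6530) = 0.814d, z = 0.814d/0.1278 = 6.4d. The common baseline still gains.

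**The case against.** The strongest reply is that nothing here is wrong. A random coefficients model with arm-specific intercept and slope is a standard trajectory model, the aim is exploratory, the equation is an example, and the final parameterisation may sit in an analysis plan that is not shown. This limits the weight of the point. It does not remove it, because the printed equation and decision rule are what the article offers, and a better version uses the same data.

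Several stronger readings are tempting and should be resisted:
- A reader might infer that the model produces false positives. It does not: the slope shift exists only conditional on an observed imbalance, can go either way, and averages to zero.
- A reader might take the statement that detectable effects "vary as a function of the correlation between pre-treatment and follow-up measures" as proof of a baseline-adjusted analysis. It proves nothing, since the precision of the arm-specific slope also depends on that correlation. Only the printed values discriminate. They match a baseline-adjusted mean rather than a slope, and the slope with a common baseline mean does not reproduce them either.
- A reader might argue that about 28 randomised groups make large baseline gaps likely. Between-group variation would enlarge chance gaps, but the article gives no intracluster correlation and the figures above ignore clustering.
- β0k has a true value of zero only if time is zero at week 0, and the coding is not stated. With both terms free, the arms may differ at week 0 under any coding, so the criticism stands, but the coding matters for the remedy. If the true effect plateaus as in step 5, the linear fit also gives a non-zero intercept difference (0.750d − 0.691d × 0.4038 = 0.47d), although the arms are equal at baseline.

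**Conclusion.** The point holds as one of efficiency and consistency. The example Aim 3a equation ignores the fact that baseline precedes allocation and drops the adjustment used in Aims 1 and 2. The slope test is valid, with 5% type I error over randomisations. The loss is modest at the only correlation the article reports and becomes large only towards the low end of its own range. That correlation, 0.68, is the pilot pre-post value for depressive symptoms. None is given for RCMAS, for PCQ or for week 52, so the loss for those outcomes is unknown within the range shown. The conditional shift from a typical baseline gap is small. Its direction favours whichever arm started worse.

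The sizes rest on compound symmetry or the assumed random-slope values, two-sided testing and independence between families. This is a worthwhile improvement to an exploratory analysis. It does not touch the primary result.

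**What to change.** In the Exploratory aim 3a equation, state that time is coded zero at week 0, delete β0k and keep β1k × Time, so that both arms share one baseline mean. Apply this to CDI, RCMAS and PCQ.

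The alternative of entering the baseline score as a covariate, with weeks 8, 24 and 52 as outcomes, is acceptable but not equivalent. β1k would then measure only divergence after week 8, and an effect fully present at week 8 and maintained would give β1k = 0. If that route is taken, the decision must rest on the arm effect at those visits and not on β1k alone.

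Statistical power should also say which 12-month contrast its detectable effects refer to, since they match a baseline-adjusted mean of three follow-ups and not a slope.

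The cost is one term in the equation and a sentence or two of text. No extra data or families are needed.

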#### Exploratory aim 3b

Determine whether perceived group support, adolescent gender and age, parent’s marital and socioeconomic status, and parent’s cancer staging modify the effects of treatment on child depression and anxiety. We will extend the models estimated above to evaluate key theoretically derived interaction terms. Predicted values will be plotted and, where appropriate, effect modifiers will be dichotomized to capture the region of effect modification. We will estimate standard errors and confidence intervals using bootstrap replications when indicated. Prior research with predominantly white samples suggests the intervention will reduce child depression and anxiety and parental stress to a greater extent for parents perceiving more group support, parents who are single and of low socioeconomic status, adolescent girls, older adolescents, and parents with more severe stages of solid tumor cancer.

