### Exploratory aims

Aim 3a. Determine treatment differences in trajectories of adolescent depressive symptoms, adolescent anxiety, and parental stress from baseline to 12-month follow-up.

Aim 3b. Determine whether perceived levels of group support, adolescent gender and age, parent’s marital and socioeconomic status, and parent’s cancer staging modify the effects of treatment on adolescent depression and anxiety.

Aim 3c. Determine whether pre-post changes in parent-adolescent attachment and communication mediate the association between treatment and adolescent depressive symptoms and anxiety at 6- and 12-month follow-ups.

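### Aim 3b lets modifier cut-points be chosen after the fitted effects are plotted, which tends to exaggerate subgroup contrasts and understate their uncertainty

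*Protocol article*

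**What the plan says.** The Exploratory aims section lists six modifiers: "Determine whether perceived levels of group support, adolescent gender and age, parent’s marital and socioeconomic status, and parent’s cancer staging modify the effects of treatment". The outcomes are adolescent depression and anxiety.

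The Analysis plan, under Exploratory aim 3b, gives the method in three steps:

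- Interactions first: "We will extend the models estimated above to evaluate key theoretically derived interaction terms".
- Then the plot and the cut: "Predicted values will be plotted and, where appropriate, effect modifiers will be dichotomized to capture the region of effect modification".
- Then uncertainty: "We will estimate standard errors and confidence intervals using bootstrap replications when indicated".

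The section also states expected directions in advance, such as larger effects in older adolescents, girls, single parents and families of low socioeconomic status. It gives no cut-point for age, socioeconomic status, group support or stage. It does not limit cutting to modifiers whose uncut interaction is significant, and it does not say that the bootstrap repeats the choice of cut. Under Primary aim 1, subsample analyses depend on a significant overall treatment difference, which is not a condition on the interaction.

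**The concern.** The order is explicit: fit, plot, then cut. So is the purpose of the cut, which is to match the range where the effect seems to differ. This is a stated rule, not a detail left to an analysis plan that is not shown.

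A boundary placed where the fitted effects look most different follows chance variation as well as any real modification. The contrast between the two resulting groups then tends to be too large. An interval computed as if the boundary had been known beforehand ignores the selection and is too narrow. Dichotomising also discards information that the uncut interaction already uses.

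Aim 3b is the analysis that would say which families benefit more. An age or socioeconomic threshold found this way could seem to confirm one of the stated directional predictions and then fail to replicate.

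**Working it through.** **Inputs.** From Statistical power: d = 0.38, pre-post correlation 0.68, 60 families analysed per arm, α = .05 (two-sided assumed), retention 70%. The phrase "using power = 8 and α = .05" is read as power .8, as a later sentence in that section has it. From Exploratory aim 3b: six modifiers and two outcomes. Gender is binary and marital status categorical, so four modifiers are open to a choice of cut.

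**Step 1. The plan's own figure.** The ANCOVA residual SD is √(1 − 0.68²) = 0.733. Families per arm = 2 × (1.960 + 0.842)² × 0.733² / 0.38² = 58.5, so 59 (stated: 60). Power at 60 per arm is 0.81, and 120 / 0.7 = 171.4, so 172. The stated size is reproduced. The document gives no figure for aim 3b.

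**Step 2. What a cut fixed in advance gives when the truth is zero.** A median split leaves about 30 families in each of four cells. The SE of the contrast is 0.733 × √(4/30) = 0.268 SD. The expected absolute contrast is 0.798 × 0.268 = 0.21 SD and the median 0.674 × 0.268 = 0.18 SD. This is the benchmark for pure noise.

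**Step 3. What a chosen cut gives.** Data were simulated as Post = 0.68·Pre − 0.38·T + e, with SD(e) = 0.733 and no interaction, 4,000 trials per setting. The fitted model had Pre, T, M and T×M, and the T×M term was tested. The chosen cut was the one with the largest interaction: 20th to 80th percentile in steps of ten for a continuous modifier, ages 14 to 17, or either of the two stage cuts.

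| Modifier, n | Rejects, uncut | Rejects, fixed cut | Rejects, chosen cut | Mean absolute contrast, fixed (SD) | Mean absolute contrast, chosen (SD) |
|---|---|---|---|---|---|
| Continuous, 120 | 5.1% | 5.2% | 19.6% | 0.22 | 0.45 |
| Age, 120 | 5.1% | 5.0% | 13.7% | 0.22 | 0.38 |
| Stage, 120 | 5.1% | 5.3% | 9.4% | 0.23 | 0.32 |
| Continuous, 172 | 4.8% | 5.2% | 19.5% | 0.18 | 0.37 |

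The fixed-cut contrast of 0.22 SD agrees with step 2. Monte Carlo error near 5% is √(0.05 × 0.95 / 4000) = 0.3 percentage points.

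Repeated runs with other candidate grids gave mostly 23 to 25% for a continuous modifier (29% with 61 candidate cuts), about 19 to 21% for age when more whole-year cuts were searched, and about 9 to 10% for stage. The result depends on how many cuts are searched. Full retention (n = 172) does not lower the rejection rate.

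**Step 4. Bootstrap with the chosen cut held fixed.** In 600 data sets with 300 replicates each, 95% intervals covered zero in 79%, against 94.7% for a median split fixed in advance. Monte Carlo error at 79% is √(0.79 × 0.21 / 600) = 1.7 points.

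**Step 5. A cut made only after a significant uncut interaction.** False positives stayed at 4.2 to 4.7%. In the trials that passed this condition the mean absolute contrast was 0.64 to 0.76 SD, with a true value of 0. Part of that excess comes from selecting on significance, which affects any result reported only when significant.

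**Step 6. Across modifiers, one outcome.** With fixed cuts, the chance of at least one false modifier among six is 1 − 0.95⁶ = 26%. If all four cuttable modifiers were searched and tested, it is 1 − 0.95² × 0.804² × 0.863 × 0.906 = 54%. Independence is assumed, and socioeconomic status and group support are both treated as continuous.

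**The case against.** A reader might infer that the plan tests each modifier at its best cut, so that its interaction tests run at 20 to 25% error and it will report false effect modification. The text does not support that. The interaction terms are evaluated before the plot, and nowhere does it say that the dichotomised term is tested or that its p-value counts as evidence. The cut may be meant only to display a fitted interaction.

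The size also depends on how the cut is chosen. If the plotted predictions come from a linear interaction and the cut is placed where the model-based treatment effect changes between significant and non-significant, a simulation (3,000 trials, n = 120) produced a cut in about 49% of trials. The cut term rejected in 4.1% of all trials, which is 4.1 / 49 = 8.4% of those with a cut. The median contrast was 0.24 SD, against 0.18 SD for a fixed split. On that reading the distortion is modest.

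Further, the modifiers and directions are named in advance, the aim is exploratory, gender and marital status are largely unaffected, and the article is condensed.

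Most of this stands and limits the claim. It does not remove it. Naming modifiers and directions does not fix where they are cut. A bootstrap used when indicated does not amount to repeating the selection. On every reading examined, the contrast at the chosen cut was larger than at a fixed one or was inflated by selection.

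**Conclusion.** The point holds as a raised risk. For age, socioeconomic status, group support and stage, the stated rule takes the boundary from the outcome data that then supply the contrast. With no true modification, the mean absolute contrast for a continuous modifier can roughly double, from 0.22 to 0.45 SD. The latter exceeds the 0.38 SD effect for which the trial is powered. Intervals that ignore the selection can cover 79% in place of 95%.

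If the cut term is tested without a prior condition, the error rate can rise from 5% to about 20 to 25% for a continuous modifier, 14 to 21% for age and 10% for stage. These are the upper end, because a full search over cuts does more than choosing by eye. With a prior significant uncut interaction the rate stays near 5%, but the contrast remains inflated.

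The simulations assume two-sided tests, 60 per arm and normal errors, and ignore clustering within intervention groups. The primary and secondary aims are not affected.

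**What to change.** In Exploratory aim 3b, replace the sentence on dichotomising with wording to this effect: inference on effect modification rests on the uncut treatment-by-modifier interaction, with age, socioeconomic status and group support continuous and stage ordinal. The treatment effect is shown with its confidence band across the modifier, from that same model (Johnson-Neyman display). This shows where the effect differs without a cut.

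If two groups are wanted for display, state the cut before outcome data are seen. Failing that, label the cut descriptive and repeat its selection inside every bootstrap replicate.

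This takes the modifier list as it stands. The change costs a sentence or two of wording and no extra data. The only downside is a less simple subgroup display.

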#### Exploratory aim 3c

Determine whether pre-post changes in parent-adolescent attachment and communication mediate the association between treatment and adolescent depressive symptoms (CDI) and anxiety (RCMAS) at 6- and 12-month follow-ups. Consistent with current recommended practice, potential mediators will be estimated using structural equation modeling with standard errors estimated using a large (e.g., 5000) number of replicate bootstrap samples. Variance will be partitioned into direct, indirect, and total effects for interpretation. Evidence for mediation is indicated by significant indirect effects. In addition to significance testing, we will evaluate these exploratory aims from an accuracy in parameter estimation (AIPE) framework to bracket estimated effect sizes using half-widths.

